## **12.3 Confidentiality and Privacy**

The personal information of all participants will be kept confidential and stored in a locked cabinet where the research materials are kept. Aside from members of the research group, only the supervisor from the Peking University Health Science Center and the PKU IRB has the right to read through the personal information of the participants. The participants' blood and urine samples will only be used for tests involving the research. Any leftover samples will be destroyed as biological samples on that day. Throughout the implementation of the research, all information of the participants will be marked using the participants' specific serial numbers or initials. The results of this research will be published in the form of a scientific paper, but all personal information of the participants (including their names, ages, etc.) will remain confidential.

This research will not look into the privacy of the participants. Participants can choose not to answer any questions they deem to be sensitive during the investigation.

## **13. Trial Management**

This research belongs in the topic of "Efficacy, Safety and Health Economics Evaluation of Different Salt Reduction Strategies on Cardiovascular Diseases", under the "Research of Key Nutrition and Action Intervention Techniques and Strategies for Cardiovascular Diseases" of the 2016 National Key R&D Program of China. It is sponsored by the Ministry of Science and Technology of the PRC. [name] from the PUCRI has been appointed as the principal investigator. The PUCRI will be the organization leading the project and is responsible for designing the research protocol, technical training, quality control, data analysis, conclusion and publication; the partner organizations of this research include the Changzhi Medical College in Shanxi Province, School of Public Health of Xi'an Jiaotong University in Shaanxi Province, and the Disease Prevention and Control Center of Hohhot City in Inner Mongolia. These three organizations are responsible for supplying the research sites, selecting and managing the participants, implementing the intervention strategies, and collecting research data.

## 14. Storage of Research Documents and Records

The research organization must establish research documents and record files to ensure accurate reporting, explanation, and verification. These documents are classified into two areas: (1) Original documents which record clinical data such as changes in blood pressure and safety parameters. (2) Management files of the research organization, at least including the revised versions of research documents such as clinical research protocol, CRF, and informed consent forms, approval documents of the Ethics Committee, salt substitute management records, responsibility and authorization documents of the personnel of the research sites, training records, project progress plan and its updates, meeting minutes, etc.

The research organization has to store the above two categories of documents for at least 5 years after the project ends or is terminated. No research documents can be destroyed without the written approval of both the project manager from the PUCRI management office and the principal investigator.

Project management documents such as the supervision reports and progress summary that is made by the PUCRI must be stored at the PUCRI for at least five years after the project ends or is terminated.

## Summary of Changes in Protocol Amendments

| Document History                                            |             |
|-------------------------------------------------------------|-------------|
| Document                                                    | Date        |
| Amendment 3 (Version 1.4) used for IRB continued review     | 17 Oct 2019 |
| Amendment 2 (Version 1.3) used for IRB continued review     | 16 Apr 2018 |
| Amendment 1 (Version 1.2) used for IRB continued review     | 8 Dec 2017  |
| Original Protocol (Version 1.1) used for IRB initial review | 19 Sep 2017 |

Amendment 3, 17 Oct 2019: Final version of study protocol

The summary of changes provided here describe the major changes made from Original Protocol to Amendment 3, including detailed description of changes and the sections where the changes were made as well as the corresponding rationales.

| Summary of Changes to the Protocol |                                    |                                                                                                                                                                                                                       |                                                                                                                                                                                                                                                                                                                                          |
|------------------------------------|------------------------------------|-----------------------------------------------------------------------------------------------------------------------------------------------------------------------------------------------------------------------|------------------------------------------------------------------------------------------------------------------------------------------------------------------------------------------------------------------------------------------------------------------------------------------------------------------------------------------|
| Date of amendments                 | Sections with amendments           | Description of Change                                                                                                                                                                                                 | Brief Rationale                                                                                                                                                                                                                                                                                                                          |
| Amendment 1, dated 8 Dec 2017      | Section 3
Study Design          | The number of eligible senior residential facilities enrolled in the study changed from 36 to 48. Adding Yangcheng county as the forth region. The number of regions of the study became 4 regions in Northern China. | One of the three regions could only recruit 8 facilities rather than 12 facilities that was originally planned (12 in each region). To ensure the study power and prevent any dropout in future years, the study decided to invite the fourth region to participate in the study and the total number of facilities were also increased. |
|                                    | Section 4
Participants          | Revised the inclusion criteria of eligible facilities. The least number of residents living in facilities changed from 30 to 20.                                                                                      | Improve the feasibility of the study so that more facilities could be eligible for recruitment.                                                                                                                                                                                                                                          |
|                                    | Section 5.4
Study Interventions | Revised the description of the study salt (regular salt or salt substitute) supply. All study salt was provided centrally free of cost, rather than                                                                   | Due to the funding constraints, we tried and successfully got the support from the China Salt Yulin                                                                                                                                                                                                                                      |

|                                |                                      |                                                                                                                                                                                                                                                                                                                                      |                                                                                                                                                                                                                                |
|--------------------------------|--------------------------------------|--------------------------------------------------------------------------------------------------------------------------------------------------------------------------------------------------------------------------------------------------------------------------------------------------------------------------------------|--------------------------------------------------------------------------------------------------------------------------------------------------------------------------------------------------------------------------------|
|                                |                                      | purchased by each facility.                                                                                                                                                                                                                                                                                                          | Co, Ltd, to provide free study salt, both the salt substitute and regular salt, for free throughout the 2 years of intervention period. It should also help to enhance the cooperation from the facilities.                    |
|                                | Section 10
Sample Size            | Revised the sample size. The number of clusters changed from 36 to 48. The number of participants in each facilities changed from 30 to 20. The corresponding sample size was changed from 1080 to 960.                                                                                                                              | Due to the increase in number of regions and facilities.                                                                                                                                                                       |
|                                | Section 13
Management plan        | Revised the description of the cooperative institution. Added Yangcheng Ophthalmology Hospital, Shanxi, as the forth study institution.                                                                                                                                                                                              | As given above, to increase resources for completion of the study.                                                                                                                                                             |
| Amendment 2, dated 16 Apr 2018 | Section 7
Safety consideration    | Detailed the safety monitoring plan for participants allocated to the salt substitute.                                                                                                                                                                                                                                               | To intensify the safety monitoring plan to detect the possible cases of hyperkalemia that might be induced by the use of salt substitute that contains enriched potassium, and improve the protection of participant's safety. |
| Amendment 3, dated 17 Oct 2019 | Section 7.4
Serious Adverse Event | Updated description of reporting of Serious Adverse Events. For expected and not relevant SAEs, do not need to follow the 'in-time reporting to IRB' rule, but record them and submit a summary to the IRB at the end of the study. For unexpected or study relevant SASs, still need to follow the 'in-time reporting to IRB' rule. | In response to the IRB's policy changes.                                                                                                                                                                                       |

## List of abbreviations

| Abbreviations | Definition                       |
|---------------|----------------------------------|
| BMI           | body mass index                  |
| BP            | blood pressure                   |
| DBP           | diastolic blood pressure         |
| FAS           | full-analysis set                |
| HR            | heart rate                       |
| LOCF          | last observation carried forward |
| MI            | multiple imputation              |
| PPS           | per-protocol analysis set        |
| SAE           | serious adverse events           |
| SAS           | safety set                       |
| SBP           | systolic blood pressure          |
| SS            | salt substitute                  |
| SSSC          | stepwise salt supply control     |

## **1. Introduction**

### **1.1 Background and rationale**

High sodium intake has been considered as the leading dietary risk factor for deaths and disability adjusted life-years among older adults. High-quality randomized trials to evaluate the effects of practical sodium reduction strategies are lacking.

### **1.2 Objectives**

The primary aim of the present study is to determine the efficacy of two practical and scalable sodium reduction intervention strategies on systolic blood pressure (SBP) among older adults living in senior residential facilities: (1) a stepwise reduction in the supply of regular salt to institutional kitchens and (2) replacing regular salt with salt substitute. The null hypothesis is that neither of the two sodium reduction interventions will reduce SBP. And if the effect of both interventions do exist, the interaction between SS and SSSC in lowering SBP during study period will be further analyzed.

The secondary aims are to:

- 1) evaluate the safety of these strategies, particularly risks of hyperkalemia with salt substitute and hyponatremia in those receiving either or both interventions.
- 2) evaluate whether sodium reduction intervention can reduce the risk of cardiovascular events and death
- 3) assess the cost-effectiveness and adherence of sodium reduction strategies
- 4) assess the impact of sodium reduction intervention on microalbuminuria

## **2. Study design**

### **2.1 Trial design**

DECIDE-Salt is a 2-year  $2 \times 2$  factorial, cluster randomized controlled trial testing the efficacy, safety, and cost-effectiveness of 2 intervention strategies for reducing dietary sodium intake

among older adults in residential facilities. The 2 interventions are (1) a controlled stepwise reduction of salt supply (SSSC) compared to “usual care (no reduction in salt supply)” and (2) introduction of low sodium salt substitute (SS) compared to regular salt. Each facility is randomly assigned to 1 of 4 groups: both SSSC and SS, SSSC only, SS only, and neither.

## **2.2 Eligibility criteria**

Eligible participants were  $\geq 55$  years old at entry, expected to live in the facility for at least 2 years, and signed informed consent. Persons with physician-confirmed hyperkalemia, expected absence from the facility  $>1$  month per year, or incomplete blood pressure measurement at the baseline were excluded.

The number of ineligible participants, if any, will be reported, with reasons for ineligibility

## **2.3 Outcome definitions**

The primary outcome for the study is SBP assessed as continuous variable (in mmHg) evaluated during 24-month follow-up.

Secondary outcomes:

- 1) DBP assessed as continuous variable (in mmHg) evaluated during 24-month follow-up.
- 2) 24-hour urinary sodium (in mmol/d), potassium (in mmol/d), and microalbumin excretion (In mg/d) assessed as continuous variable evaluated during 24-month follow-up.
- 3) Incidence of hyperkalemia. A new case of hyperkalemia is defined as having serum potassium  $>5.5$  mmol/L at either month 12 or 24 among participants with normal serum potassium at the baseline, regardless of clinical manifestations.
- 4) the risk of developing all-cause mortality, cardiovascular events (fatal and nonfatal stroke, fatal and nonfatal myocardial infarction, hospitalization or death caused by congestive heart failure)
- 5) ED-5Q during 24-month follow-up.

- 6) Incidence of renal dysfunction: A new case of renal dysfunction is defined as having eGFR <60 at either 12 or 24 months with normal eGFR at the baseline, regardless of clinical manifestations.
- 7) Incidence of hyponatremia: A new case of hyponatremia is defined as having serum sodium <135 mmol/L at either 12 or 24 months with normal serum sodium at the baseline, regardless of clinical manifestations.
- 8) A cost-effectiveness measure will be estimated based on the incremental cost of achieving each 1-mm Hg reduction in SBP

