## 7. Safety Considerations

### 7.1 Risk-Based Safety Monitoring and Management Plan

- **All participants will be screened for hyperkalemia and its related risk factors during the baseline investigation, Month 12 follow-up, and Month 24 follow-up.**

All participants enrolled in the trial will be tested for blood potassium and blood creatinine levels during the baseline investigation. Meanwhile, the information about the antihypertensive drugs (ACEI, ARB, potassium-sparing diuretics, etc.) taken by the participants will also be collected.

All participants enrolled in this trial will be tested once again for blood potassium and blood creatinine levels during the Month 12 and Month 24 follow-up.

- **Based on the results of the screening, any elderly who fit the clinical diagnostic criteria for hyperkalemia will be transferred to a local secondary hospital or above for further blood potassium and ECG testing. They will then be treated for hyperkalemia confirmed by the doctor. The elderly who are not diagnosed with hyperkalemia but fit any of the following conditions will be designated as the high risk group for monitoring.**

1. Participants with blood potassium  $>5.5\text{mmol/L}$ ;
2. Participants with  $15 \leq \text{eGFR} < 30\text{mL/min/1.73m}^2$  (Patients with Stage 4 chronic renal insufficiency).

The high risk group for monitoring will receive a blood potassium test every 3 months. Participants who are clinically diagnosed with hyperkalemia will be transferred to a local secondary hospital or above for hyperkalemia treatment. Participants who are not diagnosed with hyperkalemia will continue to be monitored for blood potassium 3 months later. The monitoring can be stopped temporarily should the blood potassium level of the participants  $\leq 5.5\text{mmol/L}$  in two consecutive tests. Otherwise, they will continue to be tested for blood potassium once every 3 months.

- **Blood potassium monitoring plan for the SS intervention group:**

All participants in the SS intervention group, aside from those who are confirmed to have

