**Safety set (SAS):**

SAS will consist of all randomized subjects who: 1) have baseline serum potassium measured 2) have received at least one month of study intervention, regardless of their eligibility. Subject will be analyzed according to the intervention they actually received.

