### 3.4 Missing data

No imputation will be conducted for primary analysis of primary outcome, secondary outcomes and safety outcomes.

For survival analysis, those who loses to follow-up will be regarded as right-censored and the censoring date will be the date of last encounter. If the date of occurrence of an event is not recorded, it will be imputed as the median of the date of last follow-up and the one when event reports.

For sensitivity analysis of SBP difference from baseline to 24-month SBP, 24-month SBP will be imputed using multiple imputation. The model will be:

$$Y_i = \beta_0 + \sum \beta_i X_i + e_i$$
$$e_i \sim N(0, \sigma_e^2)$$

Where  $Y_i$  is the SBP for subject  $i$  at month 24;  $\beta_0$  is the intercept;  $X_i$  is the variable for imputation;  $e_i$  is the random error.

Variables for multiple imputation of 24-month SBP includes SBP, DBP and pulse at baseline, 6 months, 12 months and 18 months, as well as residential facilities, center, age, gender, education, BMI, past history of hypertension, diabetes and coronary artery disease, lifestyle information, medication use in baseline and follow-up.

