### 5.3.2 Randomized comparisons

#### 5.3.2.1 Incidence of hyperkalemia

Only participants without hyperkalemia at baseline will be included in the study. A generalized linear mixed model accounting for clustering will be used for incidence of hyperkalemia

- 1) To evaluate the effect of SS or SSSC alone, the model will be:

The model will include intervention status as fixed effects, as well as cluster as random effects. Thus, the model would be:

$$\begin{aligned} \text{Logit}(P(y_{ij} = 1)) &= \beta_0 + \mu_j + \beta_1 x_{ij} + e_{ij} \\ e_{ij} &\sim N(0, \sigma_e^2) \\ \mu_j &\sim N(0, \sigma_{\mu_j}^2) \end{aligned}$$

Where  $i$  represents the  $i^{\text{th}}$  subjects,  $j$  represents the  $j^{\text{th}}$  cluster (facility),  $y_{ij}$  is the probability of hyperkalemia for subject  $i$  in cluster  $j$ ;  $\beta_0$  is the mean outcome in the control group;  $\mu_j$  is a cluster random effect to allow for between-cluster heterogeneity;  $x_{ij}$ , the predictor of interest, either SS or SSSC, is an indicator of the intervention for subject  $i$  in cluster  $j$  (1 indicates receive intervention while 0 indicates not receive intervention),  $\beta_1$ , the coefficient of interest, is the effect coefficient of intervention;  $e_{ij}$  is the random error for the measurement of subject  $i$  in cluster  $j$ .

2) To test the interaction effect of SS and SSSC, the model will be:

The model will include intervention status as fixed effects, as well as cluster as random effects. Thus, the model would be:

$$\begin{aligned} \text{Logit}(P(y_{ij} = 1)) &= \beta_0 + \mu_j + \beta_1 x_{1ij} + \beta_2 x_{2ij} + \beta_3 x_{1ij} * x_{2ij} + e_{ij} \\ e_{ij} &\sim N(0, \sigma_e^2) \\ \mu_j &\sim N(0, \sigma_{\mu_j}^2) \end{aligned}$$

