| 
The primary outcome for the study was the change in SBP from baseline to 2-year follow-up.
 
The primary analysis of intervention effects will use a generalized estimating equation with an exchangeable covariance structure accounting for clustering and adjustment for baseline SBP.
 | 
The primary outcome for the study is changed to SBP evaluated during 24-month follow-up.
 
A pre-specified linear mixed effects model will be performed to model repeated measures of SBP of the same individual over time.
 | 
To account for the impact of missing data due to high mortality and leaving from the residential facilities, all available follow-up data in SBP will be used instead of that just in 24-month alone. Thus, linear mixed model, which naturally fits to hierarchical data, is more appropriate than GEE in such situation.
 |
| 
Continuous secondary outcomes were changes in diastolic blood pressure; serum potassium; and 24-hour urinary sodium, potassium, and microalbumin excretion.
                                                                                                                                    | 
Like the primary outcome SBP, all continuous secondary outcomes are change to the mean level evaluated during 24-month follow-up
                                                                                                 | 
Same as above.
                                                                                                                                                                                                                                                                                                             |

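### The three binary safety outcomes are one yes/no per resident over two scheduled tests, with no account of how many tests were done, so missing tests understate the risk and can bias the risk ratio if testing differs by arm

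*Supplement*

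**What the plan says.** SAP 2.3 defines three binary safety outcomes, each as a single event over two occasions: hyperkalemia "at either month 12 or 24 among participants with normal serum potassium at the baseline", renal dysfunction "at either 12 or 24 months with normal eGFR at the baseline", and hyponatremia "at either 12 or 24 months with normal serum sodium at the baseline". Protocol V1.4, section 7.1, provides the occasions: all participants are to be "tested once again for blood potassium and blood creatinine levels during the Month 12 and Month 24 follow-up".

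For hyperkalemia, SAP 5.3.2.1 specifies a logit mixed model with one outcome per resident: "The model will include intervention status as fixed effects, as well as cluster as random effects". It has no visit index, offset or term for the number of tests. SAP 5.3.2.2 and 5.3.2.3 carry the same approach to the other two outcomes.

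The safety set (SAP 3.3) takes residents who "have baseline serum potassium measured 2) have received at least one month of study intervention, regardless of their eligibility". No follow-up test is required. On missing data, SAP 3.4 says "No imputation will be conducted for primary analysis of primary outcome, secondary outcomes and safety outcomes". It gives no rule for a resident with one normal and one missing test, or with none, and none of the six sensitivity analyses in SAP 5.7 covers this.

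The SAP does expect missing visits. Section 5.9 changes the SBP analysis to use all follow-up visits "To account for the impact of missing data due to high mortality and leaving from the residential facilities". Section 5.3.2.4 analyses mean serum potassium and sodium in the same repeated-measures way. The binary outcomes were not changed.

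**The concern.** A resident tested twice has two chances to be found positive; a resident who dies, leaves or misses a draw has one or none. When all are reduced to one yes/no, the result mixes the risk of the event with the amount of testing. The plan neither models the amount of testing nor says how partly tested residents are classified.

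Two things are at stake. The first is the absolute risk in Tables 6 and 7, which is too low if untested visits count as negative. The second is the risk ratio, which moves if one arm is tested less than the other. Hyperkalemia is the protocol's main safety index (section 6.2), so its estimate should not depend on an unstated coding choice.

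**Working it through.** The documents give no event rate, event count or power for any safety outcome, so there is no planned figure to reproduce. What follows is an illustration.

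**From the documents:** two scheduled tests; a case is a positive at either; 20% loss to follow-up, not split by arm (SAP 2.5).

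**Assumed:** risk per test p = 3% or 10%, equal in both arms and at both visits (true ratio 1.00); chance c of a second positive after a first, from c = p (independent tests) to 0.6; share o tested only once, the rest twice; tests missing at random. Ratios are SS over non-SS.

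**Step 1, target.** Risk if everyone had both tests: R = p(2 − c). With p = c = 3%: 0.03 × 1.97 = 5.91%.

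**Step 2, coding A** (any available positive is a case, all others non-cases): (1 − o)R + o·p.
- SS, o = 30%: 0.70 × 5.91 + 0.30 × 3 = 5.04%.
- Non-SS, o = 10%: 0.90 × 5.91 + 0.10 × 3 = 5.62%.
- Ratio 0.90.

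**Step 3, coding B** (once-tested negatives excluded, once-tested positives kept): A / (1 − o(1 − p)).
- SS: 5.04 / 0.709 = 7.10%. Non-SS: 5.62 / 0.903 = 6.22%.
- Ratio 1.14.

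| p | c | A, 30% v 10% | B, 30% v 10% | A, 25% v 15% | B, 25% v 15% |
|---|---|---|---|---|---|
| 3% | 3% | 0.90 | 1.14 | 0.95 | 1.07 |
| 3% | 60% | 0.94 | 1.20 | 0.97 | 1.09 |
| 10% | 10% | 0.90 | 1.12 | 0.95 | 1.06 |
| 10% | 60% | 0.94 | 1.17 | 0.97 | 1.08 |

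With 20% tested once in both arms (p = c = 3%), the ratio is 1.00 under either coding. The risk reads 0.80 × 5.91 + 0.20 × 3 = 5.3% under A and 5.33 / 0.806 = 6.6% under B, against a true 5.9%. Residents with no test, if coded as non-cases, lower A further.

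**Step 4, coding C** (all once-tested residents excluded). With tests missing at random this returns R in both arms, ratio 1.00. It fails otherwise:
- If 25-50% of SS residents positive at month 12 lose the month 24 test (5% per test, c = 0.3 to 0.6, a further 20% missing at random in both arms), a true 1.00 reads 0.66-0.86 under C and stays 1.00 under A.
- If once-tested residents have double the risk (3% otherwise, c = 0.3, 30% v 10%), the true ratio is 6.63% / 5.61% = 1.18. A gives 5.37% / 5.19% = 1.03 and C gives 1.00.

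**Step 5, one record per test.** Under the Step 2 assumptions, if the once-tested leave after month 12, each visit's risk set has the same risk in both arms and the ratio is 1.00. If half of them instead missed month 12, they enter month 24 at risk p rather than p(1 − c)/(1 − p); for p = 10%, c = 0.6 that is 10% against 4.4%. The fitted ratio is then at most 1.05 for 30% v 10% and 1.03 for 25% v 15%.

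**The case against.** A reader might infer that the codings always bias the ratio in opposite directions. They do not. That result needs unequal testing between arms, and also a rule that drops once-tested negatives but keeps once-tested positives, which the SAP nowhere proposes. With equal random loss there is no bias in the ratio, and with frailer once-tested residents A and C err in the same direction (Step 4).

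A reader might also infer that coding an untested visit as a non-case contradicts SAP 3.4. It does not. A resident with no observed value over the limit simply fails to meet the definition in SAP 2.3, and no value is filled in. This is an unstated rule, not an internal contradiction.

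The size rests on assumed inputs. Nothing in the documents reports unequal testing by arm. SAP 5.7 notes more missing data in Xi'an, but randomization was stratified by region. The milder contrast moves the ratio only to 0.95-0.97. With about 480 residents and 25 events per side, a 95% interval would run from roughly 0.6 to 1.7 before clustering. Mean potassium and sodium are analysed on repeated measures, and reasons for loss are reported (SAP 4.1).

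All of that stands and limits the point. Two facts keep it alive. A difference of 10 percentage points is 48 of 480 residents, or 2.4 facilities of 20, and SAP 3.2 foresees facilities dropping out. Also, under protocol 7.1, SS residents with a repeat high potassium are terminated from the research while other residents continue to be monitored, so loss of later tests could depend on both arm and outcome.

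**Conclusion.** The point holds in a conditional form. SAP 2.3 and 5.3.2 ignore the number of tests, and the safety set includes residents with one or none. On the natural reading, absolute risk is understated whenever tests are missing; this needs no assumption about the arms. The risk ratio is biased only if testing differs by arm, which is plausible but not documented. In the illustration it is 0.90-0.94 for 30% v 10% tested once and 0.95-0.97 for 25% v 15%, against a true 1.00. Keeping once-tested positives while dropping once-tested negatives gives 1.06-1.20. Excluding all once-tested residents is safe only if tests are missing at random. The documents support neither a fixed direction of bias nor a breach of SAP 3.4. A better analysis is available at little cost and should be adopted.

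**What to change.** Analyse one record per scheduled test (month 12, month 24) with a discrete-time mixed model, complementary log-log or logit, with visit and intervention as fixed effects and facility as a random effect. A resident contributes each test done and leaves the risk set after a first positive. Treat a resident who missed month 12 but was tested at month 24 as interval-censored, or add a sensitivity analysis without such residents. State that residents with no follow-up test contribute no record. Add numbers tested and positive by visit and arm to Tables 6 and 7; these counts would also help to show outcome-dependent exit, which the model does not remove.

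The cost is revised SAP wording and a restructured data set, with no new data. The one drawback is that the effect is stated per test interval, and the cumulative risk has to be derived from it.
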